### 3.5. Deliver Phase

This phase aims to evaluate the performance of the nurse-led, large language model-empowered agent employed to improve HBV screening and vaccination rates among inclusion health populations through quantitative and qualitative evaluations. The results will be used to iteratively optimize the agent and the intervention delivery among inclusion health populations through collaborative efforts between researchers, specialists, participants, and engineers.

*Quantitative evaluation*. Based on previous studies by the study team [3,40], HBV public health forums, and clinical liver disease expert consultations, 40 testing questions were formulated (Supplementary Material S2, Table S4), covering HBV, its symptoms, transmission routes, screening, vaccination, household isolation, and accidental exposure management. These questions will be posted to the agent and the original model for comparison. Model responses will be documented and assessed independently by two blinded hepatology specialists from two university-affiliated hospitals. To ensure the reliability of the human ratings, inter-rater reliability, including the Cohen’s kappa, will be calculated and any discrepancies will be resolved through consensus discussion.

A framework assessing the quality of information, understanding and reasoning, expression style and persona, safety and harm, and trust and confidence, referred to by the acronym QUEST, will be used to guide the evaluation [48]. First, the quality of information assesses accuracy and relevance of the model responses. To establish a clear ground truth, standard answers will be developed based on current guideline recommendations for HBV prevention, such as HBV screening tests and vaccination schedules. The accuracy of model responses will be determined by their alignment with these gold-standard answers. The relevance of the responses will be assessed by aligning them with the intent of the posted questions. The accuracy and relevance will be further quantified using automated metrics, including the F1 score, calculated by comparing the model responses against the gold-standard references. Second, the understanding and logical reasoning capabilities of the models will be evaluated to assess the extent to which the model accurately interprets the meaning of the input question and whether the generated response demonstrates sound reasoning. A 4-point rating scale will be used to score both comprehension and reasoning quality, with higher scores reflecting stronger performance. Third, the expression style and persona focus on the readability of model responses, which will be evaluated using the Chinese readability objective evaluation formula proposed by Cheng et al. [49]. It focuses on seven core factors, such as the proportion of conjunctions, sematic richness, and sentence length variation, that influence Chinese reading difficulty. A higher score indicates greater reading difficulty. Fourth, the assessment of safety and harm involves calculating the percentages of model responses that contain bias (language that discriminates against inclusion health populations), harm (misinformation that negatively impacts user decisions or behaviors toward HBV prevention), and fabricated information. Finally, trust and confidence aim to evaluate confidence in the models’ ability to generate accurate, fair and safe responses. A 4-point rating scale will be used, with higher scores indicating greater trustworthiness. Differences in these metrics between the agent and the original model will be compared using the Wilcoxon signed-rank test for continuous variables and Chi-square test for categorical variables.

*Qualitative evaluation*. The study will be tested in a randomized controlled pilot study to identify feasibility issues, refine solutions, and explore potential intervention benefits for participants’ HBV screening and vaccination behaviors. The eligible participants are inclusion health individuals who had not undergone HBV screening or vaccination. Based on Whitehead’s recommendations for the required pilot trial sample size [50], 40 participants will be recruited from two university-affiliated hospitals and their community health centers. Participants will be randomly allocated to the control group or intervention group in a 1:1 ratio using a computer-generated block randomization list prepared by an independent statistician. Allocation concealment will be ensured using sequentially numbered, opaque, and sealed envelopes. Two research assistants will enroll participants and reveal the group assignments by opening the envelopes in sequential order. Participants in the control group will receive a standard 15 min oral health education session focusing on HBV prevention, covering the importance of HBV prevention, screening procedures, vaccination schedules, and follow-up care after HBV diagnosis. Participants in the intervention group will be managed using the nurse-led, large language model-empowered agent (Table 1). Individual, in-depth, semi-structured interviews will be conducted at 1 and 6 months with participants in the intervention group. Interviews will specifically focus on exploring the overall user experience, potential technical barriers encountered during interaction with the agent, changes in their knowledge, attitudes, and behaviors related to HBV screening and vaccination, and perceived areas for improvement. Open-ended questions will be asked to encourage discussion, including the following: (i) How do you perceive the program overall? (ii) How do you feel about your interactions with the agent? (iii) What changes in HBV prevention occurred after participation in the program? and (iv) What do you suggest to improve the program? Each interview will be audio-recorded and transcribed verbatim. Thematic analysis will be used to analyze the data. The feedback from inclusion health populations will be used to refine the study. HBV screening and vaccination rates (specifically tracking one-dose, two-dose, and three-dose completion) will be assessed at the six-month follow-up. To ensure consistent data capture across both groups, these outcomes will be verified via electronic medical records. Additionally, secondary feasibility endpoints, including participant recruitment, intervention uptake, and retention rates, will be calculated. Group differences in these outcomes will be evaluated using the Chi-square test.

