*Compiling datasets regarding HBV prevention.* Guidelines, question–answer pairs, and tailored information will be used to construct datasets for HBV prevention. It will serve as a resource for model fine-tuning and can be incorporated into a retrieval-augmented generation framework to enhance the model’s knowledge of HBV prevention. This study will search HBV prevention and management guidelines from computerized decision systems (n = 2), guideline websites (n = 4), liver disease professional association websites (n = 4), and electronic databases (n = 10). Details of the search sources and keywords are presented in Supplementary Material S2 (Tables S1 and S2). Additionally, question–answer pairs regarding HBV published by open internet consultation records and authoritative organizations (e.g., China disease prevention and control centers) will also be collected. Moreover, tailored information will be created to address individual variations in HBV knowledge, health beliefs regarding HBV screening and vaccination, and barriers to healthcare access. This can be achieved by assessing individual needs using validated instruments and customizing messages based on the responses. An example of tailoring algorithms and information using messaging techniques is presented in Supplementary Material S2 (Table S3).

The datasets will be preprocessed. This includes removing invalid characters using regular expressions, standardizing medical terminologies with medical dictionaries (e.g., unifying hepatitis B virus, HBV, and hepatitis B), and assigning version identifiers for traceability. Text similarity algorithms will be applied to remove redundant information, while irrelevant or noisy content will be filtered out through manual review and natural language processing-based relevance assessment, minimizing the impact of hard negative samples.

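### The 40 test questions are not screened against the agent's training and retrieval data, and no fresh set is named for optimised versions, so the agent's advantage over the original model may be overstated

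*Protocol article*

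**What the plan says.** All references are to the protocol article.

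- **Test questions (section 3.5, quantitative evaluation).** There are three sources. The first listed is the team's earlier studies; the others appear in "HBV public health forums, and clinical liver disease expert consultations, 40 testing questions were formulated". The questions already exist.
- **Comparison (section 3.5).** "These questions will be posted to the agent and the original model for comparison". Two blinded hepatology specialists rate the responses, and accuracy is judged against a reference: "standard answers will be developed based on current guideline recommendations for HBV prevention".
- **Training material (section 3.4, compiling datasets).** Besides guidelines and tailored messages, the datasets will contain HBV question-answer pairs "published by open internet consultation records and authoritative organizations". On their use: "It will serve as a resource for model fine-tuning and can be incorporated into a retrieval-augmented generation framework". Section 3.1 lists the development phase as pending.
- **De-duplication (section 3.4, preprocessing).** "Text similarity algorithms will be applied to remove redundant information". This acts on the compiled datasets. No comparison with the 40 questions is mentioned.
- **Use of the results (section 3.5, opening).** "The results will be used to iteratively optimize the agent and the intervention delivery among inclusion health populations". Section 3.1 gives the same purpose. No second question set is named, and the article does not say which version of the agent supplies the reported comparison.

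**The concern.** A test of an adapted model against its unadapted parent is fair only if the adapted model has not been given the test items. Two routes could break that condition here.

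**Leakage.** Public forums and public consultation records are similar material: lay people asking common questions about hepatitis B. The fine-tuning areas in section 3.4 (including transmission, symptoms, screening, vaccination and family-based prevention) largely match the topics of the 40 questions. A collected pair could be a near-duplicate of a test question. It would then sit in the fine-tuning set, the retrieval store or both, and only the agent receives these.

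**Reuse.** If the agent is revised in the light of its answers to the 40 questions and then scored on them again, the second score reflects tuning to those items as well as real improvement.

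Blinding the raters addresses neither route. What is at stake is the meaning of the accuracy difference and of the percentages of biased, harmful or fabricated responses, all taken from the same 40 questions. They are meant to describe what adaptation achieves on questions the agent has not met.

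**Working it through.** The plan gives no sample-size or power statement for the 40 questions, so there is no figure to reproduce. The check has two parts: whether the text allows the two routes, and how large each could be.

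**1. Does the text allow it?**

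- Sources: one of the three test-question sources (public forums) resembles one training source (public consultation records). The overlap is partial.
- Separation: the only similarity step removes redundancy within the datasets. Nothing holds out the 40 questions or separates them from the question-answer set used in section 3.4 to select the foundation model.
- Feedback: the results drive optimisation, and no untouched set is named.

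Followed as written, the plan allows both routes. It does not say that either occurs.

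**2. Size of leakage, by assumption.**

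Inputs: n = 40 questions (section 3.5). Baseline accuracy p is 71%, the review figure for general-purpose models in section 3.3, or 60%, the selection threshold in section 3.4. The number of leaked questions k is assumed. Assume also that there is no true gain, that a leaked question is always answered correctly, and that leaked questions are of average difficulty.

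Apparent accuracy = (k + (40 − k)p)/40, so spurious gain = (k/40)(1 − p).

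| k of 40 | p = 71% | p = 60% |
|---|---|---|
| 0 | 0 | 0 |
| 4 | 0.10 × 0.29 = 2.9 points | 0.10 × 0.40 = 4.0 points |
| 8 | 0.20 × 0.29 = 5.8 points | 0.20 × 0.40 = 8.0 points |
| 20 | 0.50 × 0.29 = 14.5 points | 0.50 × 0.40 = 20.0 points |

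A leaked pair whose answer disagrees with the guideline-based reference would add less, so for a given k these values lean high.

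**3. Size of reuse, by assumption.**

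Suppose several equally good versions are scored on the same 40 questions and the best score is reported. Simulation (8,000 runs, independent scores) gives an expected excess as follows.

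| Versions scored | p = 71% | p = 60% |
|---|---|---|
| 1 | 0 | 0 |
| 3 | about 6.1 points | about 6.6 points |
| 5 | about 8.2 points | about 8.9 points |

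Scores of successive versions would be correlated, so these are upper illustrations.

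**4. Scale.** The 95% half-width of a single accuracy on 40 questions is 1.96 × √(p(1 − p)/40): 14.1 points at 71% and 15.2 points at 60%. Modest leakage is smaller than this sampling error. It would, however, favour one side systematically, and neither the test nor the confidence interval would reveal it.

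**The case against.** The strongest reply is that nothing in the article states that test items enter training, and that hold-out rules are detail a condensed article may leave to a fuller document. The first half is correct. The second does not dispose of the point. The article itself fixes one test set, a public question-answer training source, a comparison with the unadapted model, and optimisation from the results. Once the agent has been trained on a test question, no later analysis can undo it.

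Several stronger readings are tempting but not supported:

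- *The test and training questions share their sources.* Two of the three test sources, the team's studies and expert consultation, are not public question-answer collections.
- *The 40 questions are tuning items.* The article says that results, quantitative and qualitative together, inform optimisation. It does not say that the questions are re-run or that a later version's score is reported. A first-pass comparison carries no reuse bias.
- *The gain will be inflated.* Supplementary Table S4 is not shown, actual overlap cannot be checked, and it may be zero.
- *The original model cannot have met these items.* Section 2 notes that general-purpose models are trained on public data, so the base model may have met similar text. The asymmetry concerns the compiled datasets only.
- *The bench result decides whether participants are exposed.* No such condition on the pilot is stated.
- *Leakage can be set against an expected gain.* The article states none for this agent. Converting the 2.89-fold improvement in section 3.3 into one means guessing what kind of ratio it is.
- *Guideline text in both the retrieval store and the reference answers is leakage.* Supplying guideline content is the purpose of retrieval. The F1 score is already an addition to blinded human rating.

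**Conclusion.** The point holds as a risk that the plan leaves open, not as a demonstrated bias. Test and training sources overlap in part, the planned filter does not look at the test questions, and no fresh set is named for optimised versions. If near-duplicates enter the agent's data, or if an optimised version is re-scored on the same questions, the comparison is likely to favour the agent. The amount depends on the number of leaked questions and on the number of scored versions. The documents give neither, and the bias is zero if there is no overlap and only a first pass is reported. It is worth acting on because the questions already exist, the datasets do not, and prevention is cheap now but impossible after training.

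**What to change.** 1. Lock the 40 questions now. As the datasets are assembled, and before any fine-tuning, run the planned similarity filter against them. Remove near-duplicate question-answer pairs from the fine-tuning set, and from the retrieval store at least for the test run. Guideline content stays.
2. State that the 40 questions are kept out of the set used to select the foundation model.
3. Name the first-pass comparison, on a frozen agent, as the main bench result.
4. Test any optimised version on new questions, or label a re-score on the same 40 as exploratory.
5. Report how many pairs the filter removed, so that readers can judge the overlap.

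**Cost.** One more run of a filter already planned, a few question-answer pairs lost, and possibly a smaller headline gain. Removing pairs from the retrieval store permanently could thin content on topics users ask about. Limiting that removal to the test run avoids this, at the price of a small, reportable difference between the tested and the deployed agent. New questions are needed only if a later version is to be tested formally.

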### 3.3. Define Phase

This phase aims to identify effective intervention components and delivery strategies that address the key factors influencing HBV screening and vaccination among inclusion health populations. For intervention components, a systematic review and meta-analysis was performed that examined 13 databases, included 16 studies, and identified 13 nursing components that have effectively improved HBV screening and vaccination among inclusion health and general populations [14]. It recommended this study to incorporate (i) health education, counseling, and decision support to improve health knowledge, health beliefs, and informed utilization of HBV screening and vaccination; (ii) case management to address barriers to HBV screening and vaccination; and (iii) care coordination and referral to promote specialist care linkage (including HBV treatments) post-HBV screening.

To clarify delivery strategies, a mixed-method systematic review was conducted [16]. By searching 11 databases and reviewing 20 included studies, it found that large language models (i) provided equitable access to health information through internet-enabled devices, particularly for inclusion health populations; (ii) enhanced health knowledge and beliefs in preventing and managing chronic diseases, including liver diseases; and (iii) facilitated preventive health behaviors [16]. These models could be used to assist in the delivery of nurse-led intervention components, such as health education and counseling. However, the review noted a 71% accuracy rate for responses from general-purpose large language models, with adaptation strategies (including retrieval augmented generation) improving the accuracy rate by approximately 2.89 times [16]. Hence, this study will apply the model adaptation strategies to enhance its response accuracy.

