### 3.4. Development Phase

This phase aims to develop a large language model-empowered agent. It is grounded in (i) key modifiable factors influencing HBV screening and vaccination among inclusion health populations, as identified in the discover phase [3], (ii) effective nurse-led intervention components and delivery strategies leveraging large language models, as determined in the define phase [14,16], and (iii) established HBV prevention and management guidelines. The nurse-led, large language model-empowered agent will be developed with the following steps (Figure 2):

*Selection of a foundation model for the agent.* An optimal foundation model for the agent targeting HBV prevention will be selected from open-source large language models, such as ChatGLM3-6B (Zhipu AI Co., Ltd., Beijing, China). A standardized set of HBV-related question–answer pairs will be used to evaluate model performance in terms of text generation ability, inference speed, resource consumption, and coverage of HBV-specific knowledge. A model that effectively balances performances (meeting a minimum accuracy threshold of 60% on HBV specific questions) and efficiency for HBV prevention information will be selected for further fine-tuning. In addition, an optical character recognition model will be integrated to extract textual content from user-uploaded images (including HBV screening reports) to support downstream question-answering using the large language model. To address safety concerns, all uploaded reports and optical character recognition text will be processed transiently and purged immediately, thereby eliminating server storage and minimizing data retention risks. Furthermore, to enhance accessibility for users with limited literacy, a voice interaction system will be implemented. It will incorporate an automatic speech recognition model to transcribe user speech into text and a text-to-speech model to convert the generated responses into audio output, thereby enabling inclusive access to HBV prevention counseling.

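### Both systems answer the same 40 questions, but the categorical metrics are compared with an unpaired Chi-square test, which ignores the pairing and can lose power

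*Protocol article*

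**What the plan says.** Section 3.5 reports that "40 testing questions were formulated" and continues: "These questions will be posted to the agent and the original model for comparison". Each question therefore yields one response from each system. Two blinded specialists rate the responses and settle disagreements by consensus.

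The metrics are then compared with the "Wilcoxon signed-rank test for continuous variables and Chi-square test for categorical variables".

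The scale differs by metric:

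- **Bias, harm and fabrication.** Safety is assessed by "calculating the percentages of model responses that contain bias", harm or fabricated information. Each response either has the feature or does not, so these are binary.
- **Accuracy.** The rule is: "The accuracy of model responses will be determined by their alignment with these gold-standard answers". An F1 score is added. No yes/no coding is stated, although sections 3.3 and 3.4 treat accuracy as a percentage: "the review noted a 71% accuracy rate for responses from general-purpose large language models", and a foundation model is to be chosen "meeting a minimum accuracy threshold of 60% on HBV specific questions".
- **Understanding, reasoning and trust.** These use 4-point ratings. The text does not say whether they count as continuous or categorical.

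For the randomized pilot, the same section states: "Group differences in these outcomes will be evaluated using the Chi-square test".

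**The concern.** A Chi-square test on the table of system by outcome treats the 80 responses as independent. They are not: there are 40 questions, each answered twice. The agent is obtained by fine-tuning a foundation model and adding retrieval, so a question that defeats one system is likely to be hard for the other. The plan respects the pairing for continuous metrics and drops it for categorical ones in the same sentence.

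This is the plan's formal comparison of the agent with the original model on accuracy and safety. With only 40 questions there is little information to spare. The decisive information is how many questions changed from wrong to right and how many from right to wrong, and the Chi-square test does not use it.

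**Working it through.** The plan gives no significance level, power or effect size for this comparison, so there is no figure of its own to reproduce. What follows shows the size of the problem under stated assumptions.

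**Inputs.**
- From the document: n = 40 pairs (section 3.5); 71% accuracy for general-purpose models (section 3.3).
- Assumed: two-sided 5% level; accuracy coded yes/no; within-question (phi) correlation ρ from 0 to 0.5.
- Assumed: agent accuracy of 88%. This reads the 2.89-fold gain in section 3.3 as an odds ratio: 0.71/0.29 × 2.89 = 7.08, and 7.08/8.08 = 0.876. The document does not say that it is one.

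**Step 1: the variance.** With q = 1 − p, the difference in proportions has variance

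(p₁q₁ + p₂q₂ − 2ρ√(p₁q₁p₂q₂))/n.

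The Chi-square test omits the last term. With equal proportions, the true variance is (1 − ρ) times the variance the test assumes. The real type I error is then roughly 2[1 − Φ(1.96/√(1 − ρ))]:
- ρ = 0.3: 1.96/√0.7 = 2.34, giving 1.9%
- ρ = 0.5: 1.96/√0.5 = 2.77, giving 0.6%

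**Step 2: exact check.** The joint probability that both systems are right is p₁₁ = p₁p₂ + ρ√(p₁q₁p₂q₂). For 71% against 88% at ρ = 0.5, p₁₁ = 0.6248 + 0.0737 = 0.6985. That leaves 0.0115 for only the original model right and 0.1815 for only the agent right. Summing the multinomial probabilities over all tables of 40 pairs, with the uncorrected Pearson test, gives:

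| | ρ | Chi-square | Exact McNemar | Mid-p McNemar |
|---|---|---|---|---|
| Type I error, 71% vs 71% | 0 | 4.9% | 2.9% | 4.7% |
| | 0.3 | 1.9% | 2.4% | 4.3% |
| | 0.5 | 0.6% | 1.9% | 3.9% |
| Power, 71% vs 88% | 0 | 48% | 36% | 45% |
| | 0.3 | 47% | 48% | 59% |
| | 0.5 | 46% | 62% | 75% |

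With the unrounded 87.6% at ρ = 0.5, the powers are 43%, 59% and 72%.

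**Step 3: the same totals with different pairings.** Suppose the original model is right on 28 of 40 and the agent on 35 of 40. Pearson's statistic is 0.175²/(0.7875 × 0.2125 × 2/40) = 3.66, so p = 0.056 whatever the pairing. McNemar's test depends on the split of discordant questions (gained/lost):

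| Split | Exact p | Mid-p |
|---|---|---|
| 7/0 | 0.016 | 0.008 |
| 8/1 | 0.039 | 0.021 |
| 9/2 | 0.065 | 0.039 |
| 11/4 | 0.118 | 0.077 |

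**Step 4: rare safety events.** Type I error with the same event rate in both systems:

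| Event rate | ρ | Chi-square | Mid-p McNemar |
|---|---|---|---|
| 2.5% | 0 | 1.3% | 0.2% |
| 5% | 0 | 4.3% | 1.5% |
| 10% | 0 | 5.9% | 3.6% |
| 5% | 0.5 | 0.5% | 0.2% |
| 10% | 0.5 | 1.0% | 1.4% |
| 15% | 0.5 | 0.8% | 2.6% |

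Over event rates of 1% to 19% at ρ = 0, the Chi-square test's type I error never exceeds 5.9%.

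**The case against.** **A reader might infer that the test is too liberal for sparse safety counts.** Harm in 5 of 40 against 0 of 40 gives Chi-square p = 0.021 and exact McNemar p = 0.063, with expected counts of only 2.5. One table is not an error rate. Step 4 shows a type I error of at most 5.9% at zero correlation and 1% or less at correlation 0.5. For the same table mid-p McNemar gives p = 0.031, so much of the contrast is the conservatism of the exact test. This reading is not supported.

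**A reader might infer that accuracy is certainly mis-tested.** Section 3.5 does not fix its scale. If accuracy is graded or scored by F1, the signed-rank test applies and is correctly paired. The same goes for the 4-point ratings if they are handled as scores. This objection stands: the accuracy figures above are conditional on yes/no coding.

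**The gain rests on an unknown correlation.** This also stands. At zero correlation, mid-p McNemar has slightly less power than Chi-square (45% against 48%). At 0.3, exact McNemar gains nothing of note. For very rare safety events the paired test is no more powerful either; its merit there is that it matches the design.

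**The consequence is limited.** The results feed iterative improvement of the agent. No success threshold is attached to the comparison, and the reported percentages do not depend on the test. This stands and limits the weight of the point.

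**Chi-square might be shorthand for McNemar's chi-square.** The text never says so, and the same section uses the same name for the two independent randomized groups.

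**Conclusion.** The point holds. The design is paired by question, and the stated test for categorical metrics is not. Bias, harm and fabrication are affected as written; accuracy and relevance are affected only if coded as categories.

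The expected direction is conservative, with lost power, when the systems' results correlate positively by question. That is plausible but not documented. The main figures (type I error about 0.6%; power about 46% against 75% for mid-p McNemar) assume binary accuracy, a correlation of 0.5, an agent accuracy of 88% and a two-sided 5% level. The power loss shrinks as the correlation falls and is absent at zero.

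The point concerns only the bench comparison of the two systems. The pilot compares independent randomized groups, so pairing by question does not arise there.

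**What to change.** In the last sentence of the quantitative evaluation in section 3.5:

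- Replace the Chi-square test with McNemar's test on the 40 question pairs for binary metrics. Mid-p is preferable, because the exact version is itself conservative at this size.
- Report the paired difference in proportions with a 95% confidence interval. For rare safety events this will tell the reader more than any p-value.
- State whether accuracy and relevance are yes/no or graded, so that the test for each is fixed.
- State that the 4-point ratings are analysed with the Wilcoxon signed-rank test.

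The cost is a sentence or two of text. No new data, questions or ratings are needed, provided results are kept by question. Section 3.1 lists the Deliver Phase as pending, so the change can be made before this comparison is run.
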